## Abstract

**Background:**

Trapeziometacarpal (TMC) osteoarthritis (OA) is a common cause of pain and weakness during thumb pinch leading to disability. There is no consensus about the best surgical treatment in unresponsive cases. The treatment is associated with costs and the recovery may take up to 1 year after surgery depending on the procedure. No randomized controlled trials have been conducted comparing ball and socket TMC prosthesis to trapeziectomy with ligament reconstruction.

**Methods:**

A randomized, blinded, parallel-group superiority clinical trial comparing trapeziectomy with abductor pollicis longus (APL) arthroplasty and prosthetic replacement with Maïa® prosthesis. Patients, 18 years old and older, with a clinical diagnosis of unilateral or bilateral TMC OA who fulfill the trial’s eligibility criteria will be invited to participate. The diagnosis will be made by experienced hand surgeons based on symptoms, clinical history, physical examination, and complementary imaging tests.

A total of 106 patients who provide informed consent will be randomly assigned to treatment with APL arthroplasty and prosthetic replacement with Maïa® prosthesis. The participants will complete different questionnaires including EuroQuol 5D-5L (EQ-5D-5L), the Quick DASH, and the Patient Rated Wrist Evaluation (PRWE) at baseline, at 6 weeks, and 3, 6, 12, 24, 36, 48, and 60 months after surgical treatment. The participants will undergo physical examination, range of motion assessment, and strength measure every appointment. The trial’s primary outcome variable is the change in the visual analog scale (VAS) from baseline to 12 months. A long-term follow-up analysis will be performed every year for 5 years to assess chronic changes and prosthesis survival rate. The costs will be calculated from the provider’s and society perspective using direct and indirect medical costs.

**Discussion:**

This is the first randomized study that investigates the effectiveness and cost-utility of trapeziectomy and ligament reconstruction arthroplasty and Maïa prosthesis. We expect the findings from this trial to lead to new insights into the surgical approach to TMC OA.

**Trial registration:**

ClinicalTrials.gov NCT04562753. Registered on June 15, 2020.

**Supplementary Information:**

The online version contains supplementary material available at 10.1186/s13063-024-08057-1.

## Background

The prevalence of trapeziometacarpal (TMC) osteoarthritis (OA) is about 30% of people older than 50 years old, more common in women between 50 and 70 years old [1–3].

Symptoms are variable ranging from pain and swelling in the base of the thumb to weakness during thumb pinch. All of them lead to difficulties in daily living activities reducing capacity to work, especially in those that require repetitive movements of fist and clamp closure, impairing the quality of life and general health [3–6].

There is no consensus on the best treatment for TMC OA. Surgical approach is often considered in severe or unresponsive cases to conservative treatment. Numerous surgical alternatives have been described but the evidence still fails to conclusively show superiority among options [4–6]. Surgical indication preference is based on personal experience rather than published clinical evidence [4, 7, 8].

The most commonly used surgical treatment is trapeziectomy with or without ligamentoplasty and/or tendon interposition [9–12]. Patients achieve good results in terms of pain relief and movement in 85% of the cases, but without a significant gain in strength [13]. Recovery time in these procedures may take up to 1 year after the surgical procedure [14, 15]. The development of ball-and-socket prosthetic designs has been based on the premises of maintaining mobility, preventing proximal thumb migration, and improving pinch strength with faster recovery compared to other procedures [3, 14, 16, 17].

Nineteen different designs of prostheses have been described since 1979 [17]. Cebrián-Gomez et al. showed better results in abduction, adduction, compression strength, improvement in pain, Quick Dash test, patient satisfaction, and return to daily activities using Maïa TMC prosthesis compared to trapeziectomy with ligament reconstruction and tendon interposition [18]. Martin-Ferrero showed a 93% survival rate at ten years for ARPE prosthesis [19, 20], a similar design to Maïa® prosthesis [21]. A total joint replacement should be significantly better than trapeziectomy or its modifications to justify its use because of the added cost of the implant [17].

Based on this background, and taking into account the lack of evidence, we have designed a prospective randomized clinical trial to compare the clinical results, safety, and cost-utility of implant arthroplasty with the Maïa® prosthesis compared to trapeziectomy with abductor pollicis longus (APL) arthroplasty in the surgical treatment for TMC OA.

## Methods

### Objective

The primary objective of the trial is to investigate whether an arthroplasty implant is clinically more effective in reducing symptoms and improving function compared to trapeziectomy with ligament reconstruction arthroplasty in patients with TMC OA unresponsive to conservative treatment.

The secondary objectives are to determine the cost-effectiveness and cost-utility of implant arthroplasty compared to trapeziectomy with APL arthroplasty, from a National Healthcare System (NHS) and society perspective. In the longer term, we will evaluate differences in symptoms, function, radiological changes, work absence, and other health care resources in both surgical treatments for TMC OA.

### Design

The study is a single-center, prospective randomized, blinded, parallel-group superiority clinical trial comparing trapeziectomy with APL arthroplasty and arthroplasty with Maïa® prosthesis in patients with TMC OA. The results will be reported following the CONSORT (Consolidated Standards of Reporting Trials) statements [22]. The study will be conducted at the Department of Hand Surgery, Hospital Son Espases, Spain. The Standard Protocol Items Recommendations for Interventional Trials (SPIRIT) checklist was applied [23]. Ethical approval was obtained from the Ethical Committee (IB4144/20PS).

### Eligibility criteria

The eligibility criteria (Table 1) were designed to select a relatively homogeneous group of patients with TMC OA, suitable for either implant arthroplasty or trapeziectomy with APL arthroplasty.

**Table 1 Tab1:** Eligibility criteria

Inclusion criteria	Exclusion criteria
Male or female ≥ 18 years	CTS clinical findings
A clinical diagnosis of unilateral or bilateral TMC OA	De Quervain’s tendinosis in the hand to study
Unresponsive cases to conservative treatment for 3 months [24]	Any previous surgery on the affected wrist/hand to study
Eaton classification	Rheumatoid arthritis
- Stage 2	
- Stage 3	
Written informed consent provided by the patient, prior to any trial-specific procedures	Trigger Finger in the hand to study
	Clinical suspicion of local or systemic sepsis or infection
	Current or previous infection of the affected hand
	Pregnant or lactating females
	Allergy to any of the implant materials
	Known abuse of drugs or alcohol
	Involved in on-going litigation cases for their condition
	Arthritis, chondrocalcinosis

For participants with bilateral TMC OA, a study hand will be designated by the participant based on the most severe symptoms. Patients will not be allowed to enter the trial more than once.

#### Inclusion criteria

The study population will consist of adults aged 18 years and over with a clinical diagnosis of unilateral or bilateral TMC OA that failed to improve with conservative treatment including splint, for at least 3 months [24–26].

The diagnosis will be made by an experienced hand surgeon based on the presenting symptoms, clinical history, physical examination, and complementary imaging tests [27, 28].

TMC OA is defined radiologically by the Eaton Classification. Only grades 2 and 3 will be included in the study. Slight carpometacarpal joint space narrowing, sclerotic changes, and osteophytes < 2 mm on the dorsal or volar side of the trapezium define stage 2. Stage 3 includes joint space markedly narrowed or obliterated, cystic changes, sclerotic bone, osteophytes > 2 mm, and normal scaphotrapezial (STT) joint [28–30].

#### Exclusion criteria

Participants with any of the following diagnoses will be ineligible for the trial: carpal tunnel syndrome (CTS) symptoms, De Quervain’s tenosynovitis, rheumatoid arthritis, trigger finger, or previous surgery on the hand to study. Other exclusion criteria are listed in Table 1.

### Recruitment, screening process, and enrolment

Figure 1 describes the trial timeline. The patients referred to the hand surgery office for symptoms suggestive of TMC OA will be screened and assessed. Patients diagnosed with TMC OA will use a thumb abduction splint for 3 months, the first 3 weeks 24 h a day, and then at night for up to 3 months together with ergonomic measures. Unresponsive cases to conservative treatment and stage two or three of the Eaton radiological classification will be proposed to enroll.

**Fig. 1 Fig1:**
[figure not shown]
Trial timeline

Patients will be informed verbally about the trial and will be provided with an information report. The senior surgeon will answer any questions and the patient will be required to provide full written consent.

All participants will complete the baseline questionnaire prior to randomization. It includes questions regarding demographic characteristics, outcome measures, and potential prognostic factors.

### Recruitment strategy

Patients are referred to the Hand Surgery Unit by primary care physicians. All patients with thumb base osteoarthritis are evaluated by specialists in the Hand Surgery Unit of the Hospital. They are individually assessed to determine if they meet the inclusion criteria for the clinical trial. If they meet the criteria, the senior surgeon, after explaining the study, offers them all the possibility to enroll in the study. Since it is a single-center trial, patients from other centers or areas cannot be recruited unless the patient themselves requests to be seen and treated at our hospital, or is referred by another specialist. No financial or non-financial incentives are provided to the trial participants. Recruitment is expected to be completed in 5 to 6 years.

### Randomization and blinding

Patients will be randomized by the senior hand surgeon ([name]), via a remote web-based randomization system (OxMar Software, *Oxford Minimization and Randomization, an open source software*) [31], which ensures a concealed allocation sequence. Randomization will be stratified by sex and group age. Each participant will be assigned a unique identification number and a unique data case report form.

The participants and the senior hand surgeon will know the assigned treatment. The participants will have the appointments and controls as in our usual clinical practice.

The main investigator will be blinded to the treatment assignment and will collect the measures in the collection notebook, except for the radiological variables because of their association with the participant’s ID. The main investigator will assess the participant before the surgeon, on the same day in a different office.

### Operative treatment

Participants will be included in a protocol of major outpatient surgery under regional or general anesthesia depending on the anesthesiologist. Preoperative cefazolin (2 g) or vancomycin 1 g in case of allergy will be administered.

#### Group A: trapeziectomy and ligamentoplasty with abductor pollicis longus (APL) and tendon interposition

Participants randomized to Tendon Interposition Arthroplasty will undergo the technique described by Wulle [32] with a modification in the incision design:TMC approach through a dorsal V-shaped skin incision. Sharp dissection of the subcutaneous tissue down to the joint’s capsule. Careful dissection and protection of the sensory branches of the radial nerve.Approach to the joint’s capsule. At the radial border of the wound, the extensor pollicis brevis (EPB) tendon can be identified. In the proximal corner of the wound, the radial artery should be dissected and protected. The capsule is opened longitudinally between EPB and EPL with sharp dissection of all connecting ligaments along the trapezium.Excision of the trapezium. The bone can be excised in a piecemeal fashion removing the fragments with a rongeur, while protecting the flexor carpi radialis (FCR) tendon.Longitudinal split of the abductor pollicis longus (APL) tendon. Transection of the ulnar half of the APL tendon proximally as far as the incision allows.The abductor pollicis longus (APL) tendon slip is wrapped around the flexor carpi radialis (FCR) tendon from radial to ulnar using a hemostat.With the flexor carpi radialis (FCR) tendon pulled in a radial and proximal direction, the tendon slip is sutured to the FCR tendon using 3/0 non-resorbable sutures.The remaining strip of the abductor pollicis longus (APL) tendon is passed through the remnant of the dorsoulnar capsule sutured and back to the FCR. The rest of the APL is inserted between the metacarpal and the scaphoid to act as a spacer.Closure of the joint capsule using 4/0 resorbable suture. Closure in layers. Compressive bandage with a splint in thumb abduction on the first web space. Release of the pneumatic tourniquet.

#### Group B: joint prosthesis

Participants randomized to Joint Prosthesis Arthroplasty with Maïa® (Groupe Lépine ™) will undergo the standard technique described in the literature [14] and the surgical technique provided by Groupe Lépine (implant designer and distributor) for the implant with a modification in the incision design:TMC approach through a dorsal V-shaped skin incision. Sharp dissection of the subcutaneous tissue down to the joint’s capsule. Careful dissection and protection of the sensory branches of the radial nerve.Approach to the joint’s capsule. At the radial border of the wound, the extensor pollicis brevis (EPB) tendon can be identified. In the proximal corner of the wound, the radial artery should be dissected and protected. Capsule opening using a longitudinal incision.First metacarpal osteotomy. Parallel osteotomy 5 mm proximal of the base, oblique volar osteotomy to remove the volar osteophytes and to allow correct mobilization of the metacarpal to expose the trapezium. The intramedullary canal of the first metacarpal is reamed until stable bone contact is achieved. The trial metacarpal implant is placed and the correct size is confirmed radiologically. The trial is removed and the definitive metacarpal implant is placed.Resection of medial osteophyte of the trapezium and trapezial cup prosthesis placement. Medial and lateral osteophytes are removed. The middle area of the trapezium is located with an awl and verified with a fluoroscope. The trapezium is reamed with the hemispherical specifically designed burrs. The definitive component is placed, supervising that it has correct bone coverage.The neck longitude is determined through different trials, stability is verified and the final component is placed.Radiologic control and closure in layers. Compressive bandage with a splint in thumb abduction on the first web space.

### Post-operative care

All patients will be included in a same day outpatient surgery protocol, and discharged from the hospital few hours after the surgery. The post-operative pain management is a combination of ibuprofen 600 mg/12 h, paracetamol 1 g/8 h, tramadol 50 mg/8 h and omeprazole 20 mg every 24 h, taking into account the possible adverse effects or contraindications.

All participants will be asked to attend to the first appointment with a nurse 2 days after surgery, to check the wound and to change the bandage. Patients will be asked about the tolerability of the surgery and any adverse events will be recorded. The next appointment will be about 10 days later to remove stitches, maintaining the splint until 3 weeks after the surgery.

Group A participants must wear a removable abduction splint, for 3 more weeks. The patients will be instructed on how to put and remove the abduction splint to start opposition exercises. Finally, Group A participants will start a standardized rehabilitation protocol.

Group B participants the splint will be removed 3 weeks after surgery. They will be instructed on how to do opposition and strengthening exercises at home. They will not attend to rehabilitation sessions in the hospital.

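### The splint and rehabilitation schedules differ by arm up to the 6-week visit, so a splint seen there can unblind the assessor of strength and motion, and no described safeguard covers it

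*Protocol article*

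**What the plan says.** In the Protocol article, the section on randomization and blinding says "The main investigator will be blinded to the treatment assignment and will collect the measures in the collection notebook", with radiological variables as the one exception. It adds that this assessor sees each participant ahead of the surgeon, on the same day and in a separate office. It also says that participants and the senior surgeon know the treatment.

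The section on post-operative care has both arms "maintaining the splint until 3 weeks after the surgery". After that the arms diverge:

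- Group A: "Group A participants must wear a removable abduction splint, for 3 more weeks", with instruction in putting it on and taking it off for exercises. Then: "Finally, Group A participants will start a standardized rehabilitation protocol".
- Group B: "Group B participants the splint will be removed 3 weeks after surgery". On rehabilitation: "They will not attend to rehabilitation sessions in the hospital".

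The abstract lists outcome time points at baseline, 6 weeks, and 3, 6, 12, 24, 36, 48 and 60 months, and says "The participants will undergo physical examination, range of motion assessment, and strength measure every appointment".

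The skin incision is worded identically for the two operations (for Group B: "TMC approach through a dorsal V-shaped skin incision"), so the scar should not identify the arm.

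**The concern.** Strength and range of motion are measured by an examiner, and an examiner who knows the operation can encourage, position or read differently without intending to. That is what the blinded assessor is there to prevent. The article takes care over two possible leaks, the radiographs and contact with the surgeon. A third leak, the patient's visible aftercare, is left open. For three weeks before the first outcome visit only one arm is scheduled to wear a splint, and only that arm is sent on to formal rehabilitation.

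At stake is the credibility of the secondary comparisons of grip, key pinch, pulp pinch and goniometry. The article's background gives mobility and pinch strength as reasons why ball-and-socket designs were developed, so readers will look at these results even though they are not primary.

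**Working it through.** The point rests on schedule arithmetic and on reading three sections of the Protocol article together. No sample-size or power figure enters it.

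**Inputs**

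- Splint in both arms: to week 3 (post-operative care).
- Additional splint in Group A: 3 weeks (post-operative care).
- First postoperative outcome visit: 6 weeks (abstract). The wound check 2 days after surgery and the stitch removal about 10 days later come earlier, but they are not among the listed outcome time points.
- Order at each visit: assessor first, then surgeon (randomization and blinding).

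**Step 1: planned end of splinting**

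- Group A: 3 + 3 = 6 weeks, or 6 × 7 = day 42.
- Group B: 3 weeks, or 3 × 7 = day 21.

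**Step 2: set beside the 6-week visit.** The article gives no visit window, so both sides of day 42 have to be considered.

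| Timing of the 6-week visit | Group A | Group B |
|---|---|---|
| On or before day 42 | within the scheduled splint period | out of the splint since day 21 |
| After day 42 | may be out of the splint; rehabilitation follows | out of the splint; no hospital rehabilitation |

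In the first row a splint identifies Group A. In the second row the splint may be gone, and the remaining cue is rehabilitation, which the assessor would learn of only if the patient mentioned it.

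**Step 3: the visit order.** Seeing the assessor first keeps the surgeon's remarks from reaching the assessor. If the splint is discontinued at the surgeon's 6-week review, which is a possible reading but is not stated, the same order means that the assessor meets a Group A patient while the splint is still in use.

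**Step 4: how far it could reach.** The later scheduled visits are at 3, 6, 12, 24, 36, 48 and 60 months, which is 7. The same role collects the measures at all of them, so knowledge gained at 6 weeks could persist.

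**Step 5: which outcomes are exposed**

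| Outcome | Source | Exposed by this route? |
|---|---|---|
| VAS pain (primary) | mark made by a patient who knows the treatment | no |
| Quick DASH, PRWE, EQ-5D-5L | completed by the same patient | no |
| Grip, key pinch, pulp pinch | examiner | yes |
| Goniometry | examiner | yes |

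**The case against.** The strongest objection is that the central event is inferred. No section says that a Group A patient is wearing the splint on meeting the assessor. Its planned end coincides with the visit, it is removable, and patients are taught to take it off. This stands, and the point is therefore put as a risk.

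Three stronger readings are tempting and are not supported:

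- *Splint status separates the arms completely, 53 of 53 against 0 of 53.* That is only an upper bound. It assumes that every Group A visit falls within the splint period, that adherence is full, that the splint is on at the door and that nobody is lost, whereas the sample-size section allows for 10% loss.
- *Once broken, the blind stays broken for five years.* That requires the assessor to remember one patient's splint among 106 patients recruited over 5 to 6 years. It may happen, but the article does not say so.
- *The trial's main conclusion is compromised.* The primary VAS is marked by unblinded patients, and the discussion's list of effectiveness indicators (pain, Quick DASH, PRWE, EQ-5D-5L) includes neither strength nor motion.

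It can also be said that a condensed article leaves visit-level detail to the full protocol, which is not shown and may contain a masking step. That is fair as far as it goes. But the article does set out its safeguards (separate office, order of contact, radiographs excepted), and those safeguards do not cover a difference that it describes itself. The two sections should be reconciled where the blinding is claimed.

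**Conclusion.** The concern holds in a limited form. The stated assessor blinding and the aftercare schedule do not fit together: up to week 6 a splint is scheduled in Group A only, and the first strength and motion assessment falls at week 6, ahead of the surgeon's review. A splint seen then can reveal Group A.

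The consequence is possible observer bias in four examiner-measured secondary outcomes, at the 6-week visit and perhaps at up to seven later ones. Neither its size nor its direction can be derived from the article. The conclusion assumes that some Group A patients arrive at or before the planned end of splinting with the splint on, and that no masking step exists in a document not shown. The primary analysis is not affected by this route.

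**What to change.** Add to the section on randomization and blinding:

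1. Before entering the assessor's office, participants take off any splint and leave it outside.
2. Participants are asked not to mention their operation, splint or rehabilitation to the assessor.
3. The assessor records a guess of the allocation at 6 weeks and at 12 months, after the measurements are finished. The guesses are reported by arm with the strength and motion results.

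The guess does not restore the blind. It shows readers how far the blind held, with the caution that a later guess may reflect how well the patient has done as well as any cue seen.

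The cost is one visit instruction and one case report form field. Extra staff should not be needed, because Group A patients are already taught to remove the splint themselves. The splint and rehabilitation schedules are unchanged and are not in question here. The trial status section describes recruitment as continuing to about February 2026, so the step protects those not yet seen at 6 weeks. Participants already assessed cannot be re-blinded, and the report should say so.
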